#### Adaptation between intervention waves

First evaluation data will be available in early spring, 2018. In another representative study (see *Primary outcomes – Self-report data*) we will assess awareness of the intervention, assess which elements (e.g., flyer, website) the participants saw, where they encountered the materials, which information they can remember and whether it leads to changes in the primary outcomes. This allows identifying elements that are related to changes in vaccine hesitancy and behaviour. Effective elements will be used in the second wave (Autumn 2018), ineffective ones will be omitted.

### Evaluation of the intervention: Outcomes

The primary outcomes are indicators of vaccine hesitancy as well as uptake rates of influenza and pneumococcal vaccination. Secondary outcomes are the reduction of influenza, pneumonia, invasive pneumococcal disease and sepsis incidence in the target group. As a tertiary outcome the reduction of the economic burden of influenza, pneumonia and sepsis for the healthcare system will be assessed.

#### Primary outcomes – Self-report data

##### Hypotheses

The intervention has an impact on the target population’s vaccine hesitancy. In the course of the intervention, mean vaccine hesitancy will decrease in the intervention region as compared to the pre-intervention period. This effect is expected to be driven by individuals who encountered the materials. Factors of hesitancy that have been identified as especially relevant and that have been explicitly addressed in the intervention design should show a greater change than factors of vaccine hesitancy that have not been addressed.

##### Outcome measures

The same measures for vaccine hesitancy, further determinants of vaccination behaviour, self-reported vaccination uptake, and socio-demographic variables will be used as in the first representative study (original questionnaire [54]). In order to successfully assess the causal impact of the intervention materials on the outcome measures, the representative cross-sectional surveys will assess intervention exposure, i.e. whether participants saw the materials and where; and if so, whether they remember certain elements and contents of the intervention (e.g., flyer at the pharmacy, in a magazine, website, etc.).

##### Statistical analyses

We will compare means by inspection of 95%CIs between exposed and non-exposed participants regarding vaccine hesitancy measures and self-reported vaccination behaviour. Changes in major outcomes that have been specifically targeted by the intervention (e.g., reduction of myths, increased perception of risk, increased knowledge of sepsis) will be assessed as a function of being exposed. Among exposed participants we will conduct regression analyses of behavioural change on the interaction with the different intervention elements. We plan to analyse full cases only i.e. we use listwise deletion to deal with non-response. If conditions of listwise deletion (see above) are violated, we will use multiple imputation.

#### Primary outcome – Vaccination coverage against influenza and pneumococcus

##### Hypotheses

The intervention has an impact on the vaccination uptake in the total target population. In the course of the intervention the vaccination uptake will increase compared to a pre-intervention period and neighbouring federal states without intervention.

##### Study population

The study population comprises a sample of the statutory health-insured population in Germany (~ 85%, with the remainder mainly being privately insured). Patients will be selected from health insurance claims data. These data are generated by all statutory health insurance physicians for outpatient care and regularly transmitted to their Association of Statutory Health Insurance Physicians (ASHIP) as described previously [64]. A subset of variables including (but not limited to) birth date, sex, district of residence, type and date of administered vaccinations, and diagnosis data is transmitted on a quarterly basis to the Robert Koch-Institute (RKI). The administrative regions of the ASHIPs correspond to the federal states. Data is anonymised and an individual patient identifier is created allowing linkage of all the patient’s medical services to the patient identifier. The data on vaccination status and disease incidence is available for all statutory health insured individuals in Thuringia. In Germany about 85% of the population are statutory health insured. For the purpose of impfen60+ all individuals ≥60 years fulfilling certain inclusion criteria will be included in the cohorts. Retrospective analysis shows that for those ≥60 years, approximately 84% (ca. 560.000 individuals) of the statutory health insured proportion in Germany can be expected to be included per cohort. Hence, power calculation is not regarded as useful.

##### Outcome measures

Vaccination uptake among individuals aged ≥60 years and in the relevant subgroup before vs. after the intervention (2017, 2018, 2019) in Thuringia vs. Eastern federal states without Thuringia vs. all other federal states with available data.

##### Statistical analyses

Different methodological approaches will be considered to calculate vaccine uptake before and after the intervention. First, coverage will be calculated as the proportion of patients vaccinated per year (pneumococcus vaccination) or per season (influenza vaccination). The denominator will be taken from the KM6 statistics [65]. Second, vaccine uptake will be calculated among selected patients in a cohort approach [66]. Vaccine uptake will be calculated among those individuals who were < 60 years of age at the beginning of the observation period and turn 60 thereafter (thus have a new indication for the vaccine). For pneumococcus vaccination only, vaccine uptake will also be calculated for at-risk groups who have not been vaccinated in the last 5 years before the respective calendar year of interest and are thus recommended to receive the vaccine.

Vaccine uptake for both influenza and pneumococcus will be analysed by age, district, year/season/month and chronic underlying conditions (based on ICD-10 codes).

#### Secondary outcomes – Reduction of influenza, pneumonia, invasive pneumococcal disease (IPD) and sepsis

These outcomes will be determined by means of different methods and data sources to cross-validate the results:

a. Retrospective nationwide hospital discharge database study,

b. Population-based registry study on bloodstream infections in Thuringia,

c*.* Retrospective nationwide study based on Multidisciplinary Quality Assurance in the Healthcare System (SQG) data of community-acquired pneumonia,

d. Retrospective cohort study based on health insurance claims data,

e. Retrospective study based on health insurance claims data from Associations of Statutory Health Insurance Physicians (ASHIPs).

##### Overall hypothesis

If the primary outcome with increase in vaccination rates in Thuringia is reached in the elderly, we also expect a reduction in the incidence of influenza, pneumococcal pneumonia, invasive pneumococcal disease (IPD) and to a lesser extent sepsis and pneumonia in the target population also.
*Retrospective nationwide hospital discharge database study.*
*Hypothesis.* In comparison with other federal states, the intervention region of Thuringia shows a greater reduction and respectively lower increase in incidence of influenza, pneumonia, IPD and sepsis.*Study population*. A retrospective database study is performed using state-wide hospital discharge data from patients over the age of 60 regardless of their vaccination status from 2014 to 2019 in the German Diagnosis Related Groups (DRG) statistics, which includes nearly complete inpatient billing data from all general hospitals in Germany. All data provided in the DRG statistics are anonymous. The DRG statistics is accessible by the Federal Statistical Office via controlled remote data processing legally based on the statistical data secrecy provision under section 16 of the Federal Statistics Act (Bundesstatistikgesetz). Each case contains a main diagnosis and up to 89 secondary diagnoses, hospital mortality and length of stay, procedures and patient demographics. We identify influenza, pneumonia, IPD and sepsis in patients aged ≥60 years in Thuringia (intervention group) and in the other 15 federal states of Germany by a list of ICD-10 GM codes. Cases with unknown age and gender will be excluded from analysis. As the data source for this study includes nearly complete inpatient data from nearly all acute-care hospitals in Germany (military or prison hospitals are excluded), it practically corresponds to a population-based survey, hence power calculations are not regarded as useful.*Outcome measures.* We identify hospital-treated influenza, pneumonia, IPD and sepsis cases and deaths in the period prior to and during the intervention in Thuringia (2014–2016, 2017–2019) and describe age- and sex-standardised incidence and mortality rates for the Thuringian population as of 31 December, 2014. To evaluate the intervention effect, we will compare incidence and mortality rates in Thuringia and the other federal states considering further confounding factors as vaccination behaviour.*Statistical analyses.* Trends of age- and sex-standardized incidence and mortality rates in the years 2014–2019 will be compared between the intervention group (population of the federal state Thuringia) and the control group (population from the other federal states). The data for analysis will be complete, except for the excluded cases with unknown age and gender (less than 0.002% expected); hence no particular missing data handling is necessary.
*Population-based registry study on bloodstream infections in Thuringia.*
*Hypothesis.* The incidence of pneumococcal bacteraemia among patients aged ≥60 years in Thuringia will not increase further or will be reduced during the intervention period compared with the baseline measurement before intervention.*Study population.* To further explore the burden of IPD in Thuringia, we include all in- and outpatients aged ≥60 years regardless of their vaccination status with at least a single positive blood culture for *Streptococcus pneumoniae* registered by ALERTSNet between 1 October, 2014 and 1 October, 2019. ALERTSNet is a prospective population-based registry for bloodstream infections in Thuringia. ALERTSNet was initiated by funding from the Federal Ministry of Health and land resources in 2013, and aims to cover the whole of Thuringia by 2018 Therefore, no power calculations were performed as ALERTSNet aims to involve a complete survey of a whole federal state and not a sampling survey. All data obtained by ALERTSNet are anonymous. Data by ALERTSNet are equally protected from the access by unauthorized persons as computer systems processing personal data in the healthcare sector. Security measures include that computer systems are physically protected from unauthorized access and inlet and outlet communication connections are protected by encryption according to current industrial standards.*Outcome measures.* We identify proven cases of pneumococcal bacteraemia and associated patient data concerning age, sex and date of positive blood culture in all patients aged ≥60 years recorded by ALERTSNet since 1 October, 2014. As ALERTSNet currently does not cover all Thuringia (13.6% of Thuringia in 2014, 32.6% of Thuringia in 2015, and 50.8% of Thuringia in 2016), the increasing catchment areas have to be considered and incidence rates have to be extrapolated during the study period.*Statistical analyses.* Mean changes in the incidence and demographic data of patients with pneumococcal bacteraemia will be compared in the period prior to and during the intervention in Thuringia (1/10/2014–30/09/2017 versus 1/10/2017–30/09/2019). As there is no other population-based registry for bloodstream infections in Germany, no direct comparison to another federal state is possible. Although missing data might be possible for demographic data, they are not expected for the main outcome incidence (defined by the number of cases and date of positive blood culture for *S. pneumoniae*). Therefore, all patients reported by ALERTSNet ≥60 years with pneumococcal bacteraemia will be included in the analysis. Currently, retrospective analysis of proven cases of pneumococcal bacteraemia in Thuringia by ALERTSNet from 1 October 2014 to 30 September 2016 is completed and first prospective data for the period of 1 October 2016 to 30 September 2017 are available.
*Retrospective nationwide study based on Multidisciplinary Quality Assurance in the Healthcare System (SQG) data of community-acquired pneumonia.*
*Hypothesis.* In comparison to the whole of Germany the intervention region of Thuringia shows a greater reduction and respectively lower increase in incidence rates and mortality rates of inpatients with community-acquired pneumonia.*Study population.* To assess the incidence rates of hospital-treated community-acquired pneumonia, retrospective data published by the Multidisciplinary Quality Assurance in the Healthcare System (SQG) will be used. As community-acquired pneumonia belongs to the services for the external inpatient quality assurance requiring documentation in Germany since 2005, data on age, sex, hospitalisation, severity of disease and in-hospital mortality rate among patients with community-acquired pneumonia will be obtained annually by the responsible quality department of SQG of Thuringia and all of Germany starting in 2014. All annual data published by SQG are anonymous and available with a delay of 7 to 8 months in the subsequent year. For a population-based study power calculations are not regarded as useful.*Outcome measures.* We identify incidence rates and in-hospital mortality rates of inpatients with community-acquired pneumonia for different age groups aged ≥60 years (60–69 years, 70–79 years, 80–89 years) and assess the severity of disease (distribution of CRB-65 score) [67] in the period prior to and during the intervention in Thuringia (2014–2016, 2017–2019) compared to all of Germany.*Statistical analyses.* Trends of age-specific annual incidence rates and in-hospital mortality rates of hospital-treated community-acquired pneumonia for age groups 60–69 years, 70–79 years and 80–89 years and mean changes of CRB-65 score will be compared between the intervention region Thuringia and all of Germany in the years 2014–2019. As SQG reports completeness of data in 100%, no missing data have to be considered. Currently, retrospective data published by SQG for hospital-treated community-acquired pneumonia are available for the years 2014, 2015 and 2016.
*Retrospective cohort study based on health insurance claims data.*
*Hypothesis.* The incidences of influenza, pneumonia, IPD and sepsis are lower in people vaccinated than non-vaccinated over 60 years of age.*Study population.* To quantify the impact of influenza and pneumococcal vaccination on influenza, pneumonia, IPD and sepsis incidence and outcomes, a retrospective database study will be performed including about 300,000 persons ≥60 years, living in Thuringia, who are insured with one of the largest statutory health insurances in Germany (AOK PLUS, insured persons form about 40% of the Thuringian population). The exposed cohort group is expected to consist of about 130,000 patients with pneumococcal and/or influenza vaccination in 2014; the unexposed cohort group are patients without pneumococcal vaccination in 2008–2017 and without influenza vaccination in 2012–2017. The observation period covers the years from 2015 to 2017. The study is partly retrospective (2008–2016) and partly prospective (2017). The study was designed in 2017 and we have commenced in 2017 to acquire the data from 2008 to 2016 which are available from German SHIs with a regular delay of 9–12 months, so that the earliest time a SHI can transfer 2016 data is the end of 2017. Data preparation for statistical analysis has just begun and will not be finished before the end of 2018. As the inclusion of patients of 60 years and above in Thuringia insured with the SHI AOK PLUS practically corresponds to a complete survey, power calculations are not regarded as useful. All routine data collected by health insurances are anonymous.*Outcome measures.* Incidence rates and hospital/ICU admission rates of influenza, invasive pneumococcal diseases, pneumonia and sepsis, as well as in-hospital and long-term mortality will be compared between vaccinated and unvaccinated persons.*Statistical analyses.* Retrospective cohort study using adequate adjustment methods (multiple regression analysis, propensity score matching). The data for analysis will be complete; hence no particular missing data handling is necessary.
*Retrospective study based on health insurance claims data from Associations of Statutory Health Insurance Physicians (ASHIPs).*
*Hypothesis*. If the vaccination uptake increases considerably, related disease incidences will subsequently decrease.*Study population*. See above under primary outcome, vaccination rate.*Outcome measures*. Disease incidences for influenza and pneumococcal diseases among individuals aged ≥60 and in a to be determined subgroup of individuals before vs. after the intervention (2017 - 2019) will be compared in Thuringia vs. outside Thuringia as a function of vaccination uptake.*Statistical analyses*. The health insurance claims data include ICD-10 codes assigned by the physicians specifically for influenza and pneumococcal diseases and disease-related unspecific clinical syndromes. A number of ICD-10 codes that represent the clinical syndromes acute-respiratory infection and influenza-like illness will be selected. For pneumococcal diseases, ICD-10 codes for community-acquired pneumonia and invasive pneumococcal disease will be selected. The data for analysis will be complete; hence no particular missing data handling is necessary.The ICD-10 codes will undergo a data cleaning procedure so that they represent the specific endpoints most accurately. The disease incidence will be calculated as the proportion of diseased patients per year (pneumococcal disease) or per season (influenza disease, third and fourth quarter of calendar year plus first quarter of the subsequent year). The denominator will be taken from the statistics of statutory health insurances [65]. All routine data collected by health insurances and ASHIPs are anonymous.

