## Methods

### Study design and target population

In this intervention study, the population of the federal state of Thuringia, Germany, aged 60 years and above, forms the intervention group (*N* = 500,000). The intervention will take place in two consecutive influenza seasons (2017/18 and 2018/19, Fig. 1) and will be adapted in between. Changes in the outcomes will be compared to other German federal states and/or in a pre-post design depending on the outcome (specified below). Where possible, the analyses will follow a two-step analysis, first with an overall evaluation of the age group over 60 in general and then followed by analyses with special focus on the age group that will be identified as the main target group of the intervention.

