### Implementation and dissemination: Activities

The intervention will be implemented from September to February 2017/18 and 2018/19 (Fig. 1). The intervention will be adapted based upon the evaluation results of the first wave.

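### The hospital-discharge and pneumonia studies count January–August 2017 as intervention time, although the campaign starts in September 2017 and the registry study splits at 1 October 2017

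*Protocol article*

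**What the plan says.** The campaign dates are clear. Under Study design and target population: "The intervention will take place in two consecutive influenza seasons (2017/18 and 2018/19, Fig. 1) and will be adapted in between". Under Implementation and dissemination: "The intervention will be implemented from September to February 2017/18 and 2018/19". Nothing is scheduled before September 2017.

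The secondary outcomes define before and during in two ways:

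- **Study a (DRG hospital discharge data), Outcome measures:** "We identify hospital-treated influenza, pneumonia, IPD and sepsis cases and deaths in the period prior to and during the intervention in Thuringia (2014–2016, 2017–2019".
- **Study c (SQG community-acquired pneumonia), Outcome measures:** "in the period prior to and during the intervention in Thuringia (2014–2016, 2017–2019) compared to all of Germany".
- **Study b (ALERTSNet bloodstream infections), Statistical analyses:** "1/10/2014–30/09/2017 versus 1/10/2017–30/09/2019".

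For studies a and c, the Statistical analyses text speaks of comparing trends over 2014–2019 between Thuringia and the comparator. Study c adds mean changes in the CRB-65 severity score. Neither names a model or any other change-point.

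For the primary coverage outcome, the Outcome measures text reads "before vs. after the intervention (2017, 2018, 2019) in Thuringia". Its Statistical analyses section calculates pneumococcal coverage by calendar year and influenza coverage by season.

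**The concern.** One campaign has two start points in one protocol. The period January–September 2017 is before the intervention in the registry study and during it in the DRG and SQG studies. The article introduces these sources as a means of cross-validating one another, so their windows ought to line up.

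Months in which no one could have been exposed cannot show an effect. If they are pooled with exposed months, the estimate shrinks toward zero, and a comparison with other states does not repair this: the comparator supplies the expected rate, but Thuringia's own rate still averages exposed and unexposed time. The article already expects a smaller effect on sepsis and all-cause pneumonia than on the pathogen-specific outcomes, so there is little room for avoidable attenuation. The risk is that a real effect is missed or understated.

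**Working it through.** The article gives no power or event figure for studies a or c, so there is no stated number to reproduce. The check is a month count and a dilution formula.

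**Inputs.** During window in a and c: January 2017 to December 2019, 36 months. Campaign start: September 2017. Registry during window: October 2017 to September 2019, 24 months. The article's own influenza season (study e, ASHIP claims data): third and fourth quarters plus the first quarter of the next year.

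**Step 1: misplaced months.** January–August 2017 is 8 months. 8/36 = 22.2%.

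**Step 2: disagreement with the registry.** January–September 2017 is 9 months. 9/36 = 25% of the DRG/SQG during window is classed as before by the registry study.

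**Step 3: pre-campaign share f of the during window.** What matters is the share of expected cases, not of months. The article gives no monthly distribution, so the values below are assumptions, each spreading cases evenly over the months named.

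| Assumed timing of cases | Pre-campaign / total months | f |
|---|---|---|
| October–March only | 3 / 18 | 16.7% |
| Season quarters as in study e | 5 / 27 | 18.5% |
| All year | 8 / 36 | 22.2% |
| January–March only | 3 / 9 | 33.3% |

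**Step 4: attenuation.** Let e be the true relative reduction from launch onward, with none before. The pooled rate relative to expectation is (1 − f)(1 − e) + f = 1 − e(1 − f), so the apparent reduction is e(1 − f).

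| f | e = 10% | e = 20% |
|---|---|---|
| 16.7% | 8.3% | 16.7% |
| 18.5% | 8.1% | 16.3% |
| 22.2% | 7.8% | 15.6% |
| 33.3% | 6.7% | 13.3% |

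**Step 5: how much of the 2016/17 season is misplaced.** By the study e definition, one of its three quarters (January–March 2017). On an October–March winter, 3 of 6 months. The 2016 part stays in the before period.

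**Step 6: after realignment.** October 2017–September 2019 contains no pre-campaign month, so f = 0. The same holds for calendar years 2018–2019.

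**Step 7: pneumococcal coverage.** Calendar year 2017 holds 8 pre-campaign months and 4 campaign months (September–December).

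**The case against.** The best defence is that the split stands under Outcome measures, while the analysis text compares trends across six years. In annual trends 2017 can be seen on its own, and dilution arises only if 2014–2016 versus 2017–2019 becomes the pooled contrast or the change-point. That is a fair limit on the claim. It does not remove the defect: attributing a change in trend to the campaign needs a start point, and the only one stated for these two studies precedes the launch. This is a window fixed wrongly in the text, not a detail left open.

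Second, SQG data are annual, so a calendar-year cut follows from the source. That explains a calendar-year boundary, but not why 2017 is placed on the intervention side.

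Third, the direction is conservative and only two of five secondary sources are affected. Both are true. The error would not manufacture a benefit.

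A reader might also infer four stronger points that the article does not support:

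- **A whole pre-campaign influenza winter is counted as treated.** Only its January–March 2017 part is.
- **The effect shrinks by one third.** That is the top of an assumed range. It needs all cases to fall in January–March, equal seasons and a pooled contrast, and so could at most describe influenza, not pneumonia, invasive pneumococcal disease or sepsis.
- **The DRG and SQG results cannot be compared with ALERTSNet.** They are misaligned in time. Comparability is limited anyway, because the registry covers only pneumococcal bacteraemia, with a growing catchment and no control state.
- **2017 is the sole, contaminated baseline for coverage.** The coverage hypothesis refers to a pre-intervention period, the development section draws baseline coverage from claims data, and analysis by season and month is planned. The at-risk analysis also looks back five years. The listing of years is terse, but it does not rule out an earlier baseline.

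**Conclusion.** The split in studies a and c is wrong as written: it contradicts the stated campaign dates and the registry study's cut. The firm figure is 8 of 36 months, or 22%.

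The effect on the estimate is conditional. If the stated split is the contrast or change-point, an assumed 17–33% of the effect is lost, so a true 10% reduction shows as about 6.7–8.3%. This assumes no effect before September 2017, full effect afterwards and similar seasons. An unusually heavy or light early 2017 could move the share outside that range.

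For the primary coverage outcome the point is narrower: calendar year 2017 is a mixed year for pneumococcal vaccination and should not stand as the before year.

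**What to change.** - **Study a (DRG):** where admission dates allow, define before as up to 30 September 2017 and during as 1 October 2017 to 30 September 2019, as the registry study does. Beginning at 1 October 2014 would keep whole seasonal years on both sides. If dates are not available, use the study c rule.
- **Study c (SQG):** treat 2017 as a transition year and compare 2014–2016 with 2018–2019.
- **Pneumococcal coverage:** do not use calendar year 2017 as before. Use the planned analysis by season or month, with named pre-campaign data as the baseline.

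The cost is a re-cut of existing data and a sentence in each section. The SQG post-period falls from three years to two and loses September–December 2017. The October cut leaves one campaign month, September 2017, in the before period; from October 2014 that is 1 of 36 months (2.8%). It also removes October–December 2019, for which no wave is planned; the annual SQG data would still contain those months.

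The timing is favourable. The status section says evaluations other than the surveys are still pending, and the SQG data in hand stop at 2016, so the change can be recorded before the results for these studies are known.

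### The hospital-discharge sub-study names vaccination behaviour as a confounder of the intervention effect without limiting it to pre-intervention values, although uptake is the path through which the campaign should act

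*Protocol article*

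**What the plan says.** The sentence is in the protocol article under Secondary outcomes, Retrospective nationwide hospital discharge database study, Outcome measures. After stating that the aim is to evaluate the intervention effect, it continues: "we will compare incidence and mortality rates in Thuringia and the other federal states considering further confounding factors as vaccination behaviour". Vaccination behaviour is the only further confounder named, and no calendar period is attached to it. The preceding sentence covers both 2014–2016 and 2017–2019.

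The hypothesis under test in this sub-study is that "the intervention region of Thuringia shows a greater reduction and respectively lower increase in incidence of influenza, pneumonia, IPD and sepsis", in comparison with the other federal states.

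Three other places say how the campaign is expected to reach that result:

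- Primary outcome, vaccination coverage, Hypotheses: "The intervention has an impact on the vaccination uptake in the total target population".
- Overall hypothesis, under Secondary outcomes: "If the primary outcome with increase in vaccination rates in Thuringia is reached in the elderly, we also expect a reduction in the incidence" (for the target diseases).
- Secondary outcomes, study on claims data from the Associations of Statutory Health Insurance Physicians: "If the vaccination uptake increases considerably, related disease incidences will subsequently decrease".

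The Statistical analyses text of the discharge sub-study mentions only a comparison of age- and sex-standardised trends over 2014–2019. It does not say whether or how vaccination behaviour enters.

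**The concern.** A confounder affects the outcome and is associated with the exposure without being a consequence of it. By the protocol's own hypotheses, uptake after launch is a consequence of the exposure and lies between it and disease. Holding it equal between Thuringia and the other states asks whether the campaign lowers incidence by some route other than vaccination. That is not the hypothesis of the sub-study, and the protocol proposes no such route.

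This sub-study compares Thuringia with all 15 other states on hospital-treated influenza, pneumonia, invasive pneumococcal disease and sepsis. A plausible population effect here is small, so an estimate adjusted for concurrent uptake could come out null and be read as failure of a campaign that had in fact worked.

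**Working it through.** The protocol states no effect size, power or coverage figure for this sub-study, so there is no figure of the plan to reproduce. The check has two parts.

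**1. Causal order, from the text.** The coverage hypothesis gives campaign → uptake. The overall secondary hypothesis and the claims-data hypothesis give uptake → incidence. Together they place vaccination behaviour after September 2017 between exposure and outcome. State coverage in 2014–2016 precedes the campaign and cannot be changed by it, so it may serve as a baseline covariate. The quoted sentence does not separate the two.

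**2. Size of the loss if concurrent coverage is adjusted for.** All inputs are assumptions: baseline coverage c = 0.40, gain d = 0.05 or 0.10, vaccine effectiveness VE = 0.20, 0.40 or 0.60, and an effect on incidence only through coverage. With incidence proportional to 1 − VE × coverage, the true rate ratio is

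RR = (1 − VE × (c + d)) / (1 − VE × c).

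A simulation compared this with two regressions. It had 16 states and the years 2014–2019, one treated state from 2017, state and year effects, and 300 repetitions. Baseline coverage varied between states with a standard deviation of 8 points and from year to year with one of 1 point. The noise on log incidence had a standard deviation of 0.005.

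| d | VE | True RR by formula | RR, no uptake adjustment | RR, adjusted for concurrent coverage |
|---|---|---|---|---|
| 0.05 | 0.20 | 0.91/0.92 = 0.989 | 0.989 | 1.000 |
| 0.05 | 0.40 | 0.82/0.84 = 0.976 | 0.977 | 1.000 |
| 0.05 | 0.60 | 0.73/0.76 = 0.961 | 0.960 | 0.999 |
| 0.10 | 0.20 | 0.90/0.92 = 0.978 | 0.978 | 1.000 |
| 0.10 | 0.40 | 0.80/0.84 = 0.952 | 0.952 | 0.999 |
| 0.10 | 0.60 | 0.70/0.76 = 0.921 | 0.921 | 0.997 |

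The unadjusted pre/post comparison recovers the true effect and the adjusted one sits at about 1. The near-null result in the last column follows from assuming full mediation and coverage measured without error. The table shows the mechanism and is not a forecast.

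Partial mediation lessens the loss. With d = 0.05 and VE = 0.50, RR = 0.775/0.800 = 0.969, a 3.1% reduction. If only half of the log rate ratio ran through uptake, the adjusted ratio would be √0.969 = 0.984, so half the effect would remain.

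**The case against.** The strongest counter-argument is that the plan, as written, commits to no such adjustment. The quoted words are under Outcome measures, and *considering* is not the same as conditioning. The Statistical analyses text is the operative part, and it names no regression and no vaccination covariate. Nor are vaccination data among the variables listed for each discharge case. Patients enter whatever their vaccination status ("patients over the age of 60 regardless of their vaccination status from 2014 to 2019"), so an adjustment would have to bring in aggregate coverage from elsewhere. Vaccination behaviour might also simply mean long-standing coverage differences between states, which is a legitimate baseline concern. Finally, this is one of five data sources meant to cross-validate each other, and the community-acquired pneumonia comparison with all of Germany names no vaccination adjustment.

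Much of this stands. A reader might infer that the planned analysis will remove the campaign's effect, or that all of it is adjusted away. The document supports neither: the specified trend comparison retains the total effect, and complete loss needs both adjustment for concurrent coverage and full mediation.

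The label itself is not answered. The sentence defining how the intervention effect will be evaluated calls the mediator a confounder, and nothing restricts it to the years before launch. The silence of the analysis text leaves the two parts unreconciled. Elsewhere the protocol plans to examine incidence as a function of uptake, so a mechanism analysis could have been declared here, but was not. Adjustment is also feasible, because the project obtains uptake by federal state, where data are available, from claims data on the statutorily insured (about 85% of the population). This goes beyond the usual detail that an article leaves to an analysis plan, because the role it assigns to the variable is wrong as stated.

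**Conclusion.** The point holds in a limited form. Naming vaccination behaviour as a confounder of the intervention effect, without a pre-intervention limit, contradicts the protocol's own hypotheses. The consequence is conditional: it affects any estimate adjusted for 2017–2019 coverage, and not the age- and sex-standardised trend comparison that the analysis text specifies.

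Such an estimate would lose most or all of the part of the effect that runs through uptake. Under the assumed inputs, rate ratios of 0.92–0.99 move to 0.997–1.000. The direction follows from the causal order in the text. The size rests on assumed coverage, gain and effectiveness, on full mediation and on accurately measured coverage. The loss would be smaller under partial mediation and absent if only pre-intervention coverage were used.

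**What to change.** In the Outcome measures text of the hospital discharge sub-study:

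- Delete vaccination behaviour as a confounder of the intervention effect, or restrict it to state-level coverage in 2014–2016. In a pre/post comparison between states, constant differences in coverage level cancel, so a baseline term is useful only if coverage is thought to predict different trends.
- State that the effect estimate is the pre/post contrast between Thuringia and the other states, without any measure of uptake after launch.
- Report any model that includes concurrent uptake separately, labelled as a mediation or mechanism analysis, with the source of the aggregate coverage named.

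The Statistical analyses text should repeat the same wording so that the two parts agree. The cost is about one sentence, with no new data. The protocol reports that evaluations from sources other than the surveys were still pending at submission, which left room to make the change before analysis.
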